### Determining progression to the definitive trial

Progression to a full trial application will occur if minimum success criteria are achieved in key feasibility aims and objectives, and/or if solutions can be identified to overcome any issues. These criteria will be finalised in discussion with the TSC. A red, amber, green system will assist the decision-making progress, with red indicating ‘Stop’, Amber indicating ‘Discuss and Modify’ and green indicating ‘Go’. The anticipated progression criteria are detailed in table 3.

**Table 3 T3:** Progression criteria

Criteria	RAG rating
60 participants recruited within a 7-month recruitment window.	Red: <60% Amber: 60%–80% Green: >80%
Percentage of participants randomised to intervention group non-compliant in wearing the shorts (non-compliance—wearing the shorts for less than 6 hours/day or total of 42 hours/week).	Red: >70% Amber: 50%–70% Green: <50%
Percentage of participants completing primary outcome measure (NRPS) at 24-week follow-up.	Red: <60% Amber: 60%–80% Green: >80%
*Percentage of participants completing secondary outcome measures at 24-week follow-up in (in the following order of priority (EQ-5D-5L, SF-36, PGQ, ICIQ).	Red: <60%, Amber: 60%–80%, Green: >80%
Evidence to suggest efficacy, that is, that the support shorts hold promise as an effective intervention, demonstrated by an 80% CI that indicates plausibility of the between group difference in the primary outcome measure being ≥1 point, on the NRPS.	N/A
Total resource estimated to conduct the definitive trial within levels likely to attract funding.	N/A

*This progression criteria relates to the selection of outcome measures to be used in a definitive trial. It does not influence the decision as to whether or not there should be progression to a definitive trial.

CI, confidence interval; ICIQ, International Consultation on Incontinence Questionnaire; NRPS, Numerical Rating of Pain Scale; PGQ, Pelvic Girdle Questionnaire; SF-36, Short Form-36.

## Ethics and dissemination

The EMaPP trial has received approval from the: Research Ethics Committee (REC) (REC reference number: 21/WM/0155); Health Research Authority (HRA); and confirmation of capacity and capability from the Research and Development departments of the participating centres. Any amendments to the protocol will be discussed with the sponsor and submitted to HRA/REC for approval.

Dissemination will target users, clinicians and researchers. The results will inform the design of the anticipated definitive trial. It will not inform clinical decision-making since clinical and cost-effectiveness cannot be determined at this level. Dissemination, regardless of outcome will be via: publication of results in a peer-reviewed journal, a funding proposal for a full scale effectiveness trial (if progression criteria are met), lay orientated research feedback events and a lay summary for trial participants, staff and the general public and via conference presentations at grass roots physiotherapy events and research conferences. The study report will be accessible on the study web page (https://www.plymouth.ac.uk/research/emapp-trial), as will the trial protocol and statistical analysis plan. The protocol has been written and published in line with Standard Protocol Items: Recommendations for Interventional Trials guidelines.^27^ Publications will follow CONSORT guidance for feasibility trials,^28^ and the template for intervention description and replication) guidelines.^29^ Authorship of the intended articles will be the study team; professional writers will not be used.

### Changes post-trial registration

Initial inclusion criteria included a ceiling to pain chronicity of 2 years. This was amended to include women with pain persistence of >2 years, following discussion with the trial steering committee, to optimise recruitment. In addition, an ethical amendment was approved for the clinical care team to contact women who had been sent a PIS but had not completed the attached reply slip; to understand the reasons behind this.

### Economic evaluation

The resources required to provide the intervention will be assessed and a framework established for a future cost-effectiveness analysis alongside a definitive RCT. Data on intervention resources will be collected via within-trial reporting, including participant-level contact and non-contact time and training for delivery staff. Participants will self-report health, social and wider care resource use, using the Resource Use Questionnaire. Participants will complete the EQ-5D-5L (the anticipated primary economic outcome measure in a full trial), and quality adjusted life-years (QALYs) will be estimated over the follow-up period. The appropriateness of the Short Form-6 Dimension (SF-6D), based on the Short Form-36 (SF-36) for estimating QALYs will be explored. The economic evaluation methods will be developed to provide a future policy-relevant cost-effectiveness analysis of the intervention in the context of the UK NHS/Personal Social Services.

### Data management and analysis

Detailed data management activities are described in a separate data management plan. PenCTU staff will monitor completeness and quality of data throughout the trial. No imputation of missing data will be undertaken.

#### Quantitative

A detailed statistical analysis plan will be finalised ahead of trial database locking. A CONSORT diagram will display data from screening, recruitment, consent and follow-up logs and be used to generate estimates of eligibility, recruitment, consent and follow-up rates. Completion rates will be estimated for outcome measures at each time point, including the health, social and wider care resource-use data. Recruitment and retention rates will be accompanied by 95% CIs, to inform assumptions for planning the definitive trial. Adherence data (wear time) will contribute to evaluation of intervention acceptability/feasibility and evaluated as total hours and as a percentage of total possible daytime wearing time (12 hours/day). The percentage of week’s participants wore the shorts for a minimum of 42 hours a week, and the percentage of days participants wore the shorts for a minimum of 6 hours a day, will be summarised.

All outcomes will be summarised by allocated group at each follow-up with appropriate descriptive statistics. Between-group differences will be reported with 80% CIs in addition to 95% CIs, with particular focus on change in pelvic girdle day-time pain at the primary end point of 24 weeks. According to the 2008 Initiative on Methods, Measurement, and Pain Assessment in Clinical Trials (IMMPACT) consensus statement,^26^ changes of one point represent minimally important decreases in pain using the NRPS of pain intensity. We will inspect the CI of the between group difference to see if there is evidence of a plausible signal of efficacy. Estimates of the variability of outcome measures and the correlation between baseline and follow-up outcome measures will inform the sample size calculation for a future definitive RCT.

#### Qualitative

Thematic analysis will be used for the telephone interview data using NVivo V.12 software for organisation and analysis (QSR International, Southport, UK, July 2021). Braun and Clarke’s six-phase process will be used: (i) data familiarisation; (ii) coding; (iii) generating initial themes; (iv) reviewing themes; (v) defining and naming themes and (vi) writing up to identify patterns of meaning within the data sources. Initial themes will be refined by two researchers to maximise credibility and dependability.

Interviewees will be invited to review a draft of the analysis to ensure accurate representation of their views/experiences.

## Discussion

This is the first RCT to explore the feasibility and acceptability of a novel customised pelvic orthosis in the management of chronic PGP in the postpartum period. There is a lack of evidence to support the management of this condition beyond the first 8 weeks post partum. This orthosis has already shown promise as an intervention during pregnancy,^18^ and in a replicated case series study of eight women post partum.^19^ This trial aims to serve as a starting point to investigate the effectiveness of this orthosis in the management severe chronic PGP post partum.

Some aspects of the study design are noteworthy. All trial procedures and intervention delivery are undertaken remotely; described as a virtual trial.^30 31^ This replicates current practice, mitigates the risk associated with face-to-face appointments during the COVID-19 pandemic and ensures trial delivery in the event of a lockdown. It is also a potentially more efficient approach.^31^ Because some participants may not be able to participate in a fully virtual trial, to optimise generalisability provisions have been made to provide a non-virtual format when this is preferred by the participant. Monitoring of the proportion of women who choose a non-virtual approach will further inform the future trial design.

All outcome measures collected at follow-up time points (apart from adherence to wear time in the intervention group) are patient reported outcome measures (PROMs), and via a web-based application. This approach was chosen on the basis of PPIE input, the rationale being to minimise participant burden. The collection of PROMs minimises the influence of the research team on data collection. Recommendations from Mercieca-Bebber,^32^ have been used to improve PROMS data collection during this trial, such as reducing free-text options in questionnaires, flexible data entry and text/email reminders to enhance data completeness. With regard to wear-time adherence data, this too is collected remotely using the Orthotimer temperature sensor; with the added advantage of providing detailed and objective data which is otherwise challenging to reliably collect via methods such as patient diaries.

The qualitative interviews are also undertaken via remote means. This decision was informed by PPIE discussions, aiming to reduce participant burden in terms of travel time and inconvenience; particularly important considerations for people in pain and looking after young children.

The self-report depression questionnaire, Edinburgh Postnatal Depression Scale (EPDS)^33^ is used to assess post-natal depression. If a score of >12 points (indicative of depression) is recorded, an email to the research team is triggered to contact the participant and their GP, thereby to ensuring duty of care is upheld. The data collected will have the added advantage of increasing understanding of the prevalence of post-natal depression in this population; currently an under-researched area.

Persistent PGP is difficult to manage with the aetiology of the condition,^34 35^ and the mechanism of action of pelvic orthotics under debate. One factor that has recently been under the spotlight within this group and may represent a possible mechanism of action for an orthotic, relates to changes in somatoperception (the perception of size and shape), with evidence pointing to an altered explicit somatoperception in both the peri-natal^36^ and post-natal period.^37^ This study has included explicit (via the Freemantle Back Awareness Questionnaire (FreBAQ)) and implicit (measure of 2PE) measures of somatoperception, as recommended by Viceconti *et al*.^38^ It is the first to study both types of somatoperception in parallel during an interventional trial.

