**Trial status:**

Currently recruiting.

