#### Clinical outcome measures

A battery of standardised, patient reported outcome measures, together with demographic and diagnostic characteristics (birth details, pain history, Beighton Score^20 21^ and two point estimation (2PE) Task,^22 23^ will be collected at baseline. A selection of outcome measures will be repeated fortnightly and at 12 and 24 weeks after the first-intervention session to map in more detail the trajectory of pain over the trial timeline (table 2). All patient reported outcome measures will be reported directly by the participants via the web-based application. At each time point, participants will automatically receive five text/email reminders (one per day) if the data entry has not started. All patient reported outcome measures included within this study align with the PGP core outcome set for evaluating the effectiveness of interventions in postpartum PGP.^24^

**Table 2 T2:** Assessment schedule

Assessments	Baseline	Post-initial appointment		
		Fortnightly	12 weeks	24 weeks
Demographics, birth details, pain history	x			
Beighton score^20 21^ to determine joint hypermobility	x			
Two-point estimation task^22 23^ to determine implicit somatoperception	x			x
Pain medication use	x	x	x	x
Numerical Pain Rating Scale^25 26^	x	x	x	x
Health and Social Care Resource use Questionnaire to collect data on health, social and wider care resource use^18^	x		x	x
Edinburgh Post-natal Depression Scale^33^ to assess post-natal depression (cut-off **≥**12 points)	x		x	x
Freemantle Back Awareness Questionnaire to assess explicit body perception of the lumbo-pelvic region^36 37^	x		x	x
Pelvic Girdle Questionnaire^40^ to assess function and symptoms	x		x	x
Short-form 36^41^ to assess health-related quality of life and calculate quality adjusted life-years (QALYS)	x		x	x
EQ-5D-5L to assess health-related quality of life and calculate QALYS^42^	x		x	x
International Consultation on Incontinence Questionnaire, Urinary Incontinence—Short Form to assess level and impact of symptoms of incontinence^43^	x		x	x
Tampa Scale Kinesiophobia to assess fear of movement/kinesiophobia^44^	x		x	x
Wear-time adherence (Orthotimer)				x
Qualitative interviews				x

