#### Adverse events

Throughout the trial, all possible precautions will be taken to ensure participant safety and well-being. Participants will be monitored for adverse events throughout the 24 weeks. The likelihood of participants being harmed by either wearing the orthosis or undertaking the exercise programme (which reflects usual clinical practice) or any of the trial procedures is considered very low. Collection and reporting of adverse events will be captured via the web-based app and relate to those classified as an adverse reaction (including adverse device effects) or those which are serious. These will be collected at fortnightly intervals. On receipt of a reported reaction or serious adverse event, the CI will contact the local PI to discuss causality. All adverse events will be reported at the Trial Steering Committee (TSC) and Trial Management Group (TMG) meetings.

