#### Sample size

As this is a feasibility trial, a formal sample size calculation, based on power for detecting a clinically meaningful between-group difference in a primary clinical outcome, will not be undertaken. The trial aims to recruit 60 participants over a 7-month period. The sample size is pragmatic and determined to be large enough to provide robust estimates on the likely recruitment rates and follow-up and estimates of the variability on the proposed primary outcome to inform a future sample size calculation. The target is set to enable determination of whether it would be practicable to recruit adequate numbers in a manner conducive to implementing a reasonably costed definitive trial. A sample size of 60 will allow overall retention rate at 6-month follow-up to be estimated to within a 95% CI of approximately ±13% (±10% if retention rate is 80%). Assuming a non-differential retention rate of 80%, this should provide follow-up outcome data on a minimum of 24 participants per group.

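### The EPDS depression cut-off is ≥12 in Table 2 but >12 for the duty-of-care alert, so the two rules disagree at a score of exactly 12

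*Protocol article*

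**What the plan says.** The EPDS threshold appears in two places in the protocol article.

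- **Clinical outcome measures, Table 2.** The EPDS is collected at baseline, 12 weeks and 24 weeks. Its entry reads "to assess post-natal depression (cut-off ≥12 points").
- **Discussion.** "If a score of >12 points (indicative of depression) is recorded, an email to the research team is triggered to contact the participant". The stated purpose is "to contact the participant and their GP, thereby to ensuring duty of care is upheld". The same paragraph names a second use of the data: "increasing understanding of the prevalence of post-natal depression in this population".

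Three other statements bear on the consequences.

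- On data entry, Clinical outcome measures says: "All patient reported outcome measures will be reported directly by the participants via the web-based application".
- On safety reporting, the Adverse events section says that the events captured "relate to those classified as an adverse reaction (including adverse device effects) or those which are serious".
- The abstract gives the trial status as "Currently recruiting".

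**The concern.** The two operators classify a score of 12 differently. Table 2 counts it as meeting the cut-off for depression; the Discussion does not count it and raises no alert. Both rules describe the same construct, because the Discussion itself labels its threshold as indicating depression.

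This matters mainly for participant safety. The alert is the only response to a high EPDS score that the article describes. The questionnaire is completed remotely, so whether anyone is told depends on the operator in the software. Adverse event collection is limited to reactions and serious events and is not designed to pick up a raised score. If the application follows the Discussion literally, a woman who meets the trial's own Table 2 cut-off with a score of 12 prompts no contact by this route.

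There is also a small reporting consequence. Any statement of how common depression is in this sample depends on which operator is used.

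**Working it through.** **Inputs**

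- Cut-off in Table 2: score ≥12.
- Alert threshold in the Discussion: score >12.
- EPDS time points in Table 2: three (baseline, 12 weeks, 24 weeks).
- Recruitment target in Sample size: 60 women.
- Retention in Sample size: 80%, given for the 6-month follow-up ("Assuming a non-differential retention rate of 80%, this should provide follow-up outcome data on a minimum of 24 participants per group").
- Assumption: the EPDS is scored in whole points. The article does not state this.
- Assumption: the 80% rate also applies at 12 weeks. The article gives no figure for that time point.

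**Step 1. Compare the rules score by score**

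| Score | Table 2 (≥12) | Discussion alert (>12) | Agree? |
|---|---|---|---|
| 11 or less | below cut-off | no alert | yes |
| 12 | meets cut-off | no alert | **no** |
| 13 or more | meets cut-off | alert | yes |

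The disagreement is confined to one score. The article mentions the EPDS threshold nowhere else and does not say that a separate, higher alert threshold was intended.

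**Step 2. Count how often the rule is applied**

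- Full retention: 60 × 3 = 180 questionnaires.
- 80% retention at both follow-ups: 0.8 × 60 = 48 women at each, so 60 + 48 + 48 = 156 questionnaires.

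**Step 3. Effect of one woman scoring 12 on a reported proportion**

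- Baseline: 1/60 = 1.7 percentage points.
- 24 weeks at 80% retention: 1/48 = 2.1 percentage points.

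Steps 2 and 3 give only the scale. They do not estimate how many women will score 12; the document offers no basis for that, and none is assumed.

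**The case against.** The strongest objection is that no harm is shown. The alert is described in a Discussion paragraph of a condensed article, not in an operating procedure. The article refers to a separate data management plan and to a full protocol and statistical analysis plan, and the exact trigger would normally be specified in documents of that kind. If the software uses ≥12, the problem is one wrong character in print. This stands as a limit on the consequence: the mismatch is certain, the safety gap is conditional. It does not excuse the mismatch, because the article states the rule twice and differently, which is not the same as leaving it to another document.

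A second argument is that classification and alert thresholds may differ on purpose. The text does not support that, since the Discussion applies the depression label to its own >12 threshold.

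A third is that a woman scoring 12 might be noticed anyway, because every participant has two physiotherapy sessions. That is possible, but nothing says that the physiotherapists see EPDS scores.

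Two further points are fair. The document does not show which threshold was intended, so preferring ≥12 is a judgement, and a lower trigger means more contact with participants and GPs. And the analysis consequence is thin: the Quantitative analysis section plans descriptive summaries and names no EPDS proportion, while prevalence appears only as a side benefit in the Discussion.

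**Conclusion.** The concern holds, as a minor internal inconsistency. Table 2 and the Discussion give different rules for the same construct, and they conflict at a score of exactly 12, assuming whole-number scoring. The number of women affected is unknown.

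The safety consequence arises only if the application is programmed as the Discussion states. The reporting consequence arises only if a proportion meeting the cut-off is presented. The feasibility outcomes, the Numerical Rating of Pain Scale results and the progression criteria in Table 3 are untouched. The point is worth acting on because the threshold is tied to a duty of care and the correction is cheap.

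**What to change.** 1. Print one operator in Table 2, in the description of the alert, and in any EPDS summary.
2. Use ≥12 for the alert by default, because it matches Table 2 and errs towards contacting the woman. If the clinical lead has a reason for >12, document it and change Table 2 to match.
3. Confirm which operator the live web application uses.
4. List any participant who has already scored exactly 12 at any time point and review whether contact is needed. The article describes recruitment as under way, so the correction could still reach participants.

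The cost is a one-line text correction, one configuration check and a short data listing. If the alert moves to ≥12, there may be a few additional contacts with participants and their GPs.
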